### Data management

Data management will be done using Research Electronic Data Capture (REDCap) electronic data capture tools. REDCap^78 79^ is a secure, web-based software platform designed to support data capture for research studies, providing (1) an intuitive interface for validated data capture; (2) audit trails for tracking data manipulation and export procedures; (3) automated export procedures for seamless data downloads to common statistical packages; and (4) procedures for data integration and interoperability with external sources.

### Data analysis

For all primary outcomes, rate and corresponding 95% CI will be estimated with the method of Clopper-Pearson. Furthermore, for each estimated rate, it will be checked whether it is inside the red, amber or green zone. If at least one rate falls within the red zone, a decision against feasibility is made.

Repeated measures of the SUPA-Q Score will be analysed with a linear mixed effect model, using the score after the intervention as dependent variable, the score from the same day before intervention and the intervention group as fixed effect, and a random patient effect. For the other secondary outcomes, weight gain and EDE-Q, exploratory analysis will be done with a linear model (analysis of covariance (ANCOVA)), with the value at the end of treatment as dependent variable and the intervention group, the baseline value and AN subtype as independent variables.

All analyses will be done in the intention-to-treat population. For all feasibility outcomes, missing values will be imputed taking the reasons for dropout into account. We will not conduct interim analyses.

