### Outcomes

Primary endpoints include established measures of VR intervention feasibility^63^: acceptability will be measured with the System Usability Scale (SUS)^64^; tolerability will be measured with the Simulation Sickness Questionnaire (SSQ)^64 65^; intervention adherence is measured in minutes of completed VR exposure. We will administer all assessments on a per-session basis and use the means across sessions as dependent variables. Acceptable levels of feasibility (ie, the trial progression criteria) for the primary endpoints are defined as follows: (1) normative data for the SUS suggest that average scores below 50 indicate insufficient acceptability, and scores above 70 indicate sufficient acceptability^66^; (2) empirical evidence shows that 60–95% of participants experience some level of cyber sickness during VR exposure, as determined by an SSQ Score greater than 40.^67 68^ Given its high prevalence, we deemed that cyber sickness rates (ie, proportion of patients with an average, across-session SSQ scores≥40) exceeding 95% would clearly indicate the RCT as infeasible, whereas any rates below 60% would suggest the RCT is feasible; (3) adherence, according to our pilot data, refers to completing at least 12 min of exposure, at which point habituation onset can be observed. We reasoned that adherence rates should not be lower than 50% (ie, no fewer than half of the patients should complete the minimum amount of average exposure) and that it should ideally approach the average level estimated across other VR exposure therapies (84%^69^).

Secondary endpoints include (1) outcomes relevant to the mechanism of the intervention (ie, activity urges) and (2) clinical outcomes (to be evaluated in the full-scale RCT) as targeted by AN treatment guidelines.^21^ Activity urges will be recorded on a per-session basis using the validated state activity urges questionnaire (State Urge to be Physically Active-Questionnaire (SUPA-Q)).^55^ The clinical outcomes, monitored on a weekly basis, include changes in eating disorder psychopathology using the Eating Disorder Examination-Questionnaire (EDE-Q),^70^ as well as weekly weight gain, defined by changes in patient BMI (in kg/m²), which will be obtained from patient records.

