### Participant timeline

Because changes during the first 3–4 weeks are critical for overall AN treatment outcomes,^16^,^18^ the VR intervention or control procedure will be delivered on a weekly basis over the course of the initial four consecutive weeks of AN treatment. On admission, we will screen patient records based on diagnosis, age and BMI. Patients potentially meeting inclusion criteria will be assessed for eligibility and, if eligible and willing to participate, randomised to receive the VR intervention or VR control procedure on a weekly basis over the course of the four consecutive weeks. A weekly schedule with two sessions will be implemented as we expect daily experiences (eg, supervised meals, weighing and mirror exposure as part of regular inpatient treatment) to trigger activity urges repeatedly, thus requiring regular and repeated attendance. The proposed trial duration and frequency of visits are similar to other VR-based exposure therapies for patients with AN.^49 52 74^

At enrolment, we will record patient height and body weight, and diagnosis (based on ICD-10 criteria), and patients will be asked to complete a sociodemographic questionnaire, the EDE-Q, the CES, the FPTM-23 and a brief excessive PA interview. At the end of each week during the trial, patients will complete the SUPA-Q, the EDE-Q, and we will record patients’ current weight. After each session, patients will provide acceptability and tolerability ratings, and we will record the duration of completed exposure sessions. We will record the reasons, if sessions are terminated prematurely. At close-out, we will evaluate patient blinding in a close-out interview, and record patient weight, SUPA-Q and EDE-Q scores (see figure 2).

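### Weight and EDE-Q are recorded weekly but analysed by ANCOVA on the end value only; a repeated-measures model would use the data already collected, at almost no cost

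*Protocol article*

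**What the plan says.** All references are to the protocol article.

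- **Collection.** Outcomes describes weight gain and EDE-Q as "The clinical outcomes, monitored on a weekly basis", with BMI taken from patient records. Participant timeline confirms it: "At the end of each week during the trial, patients will complete the SUPA-Q, the EDE-Q", with weight recorded at the same time. Both are also recorded at enrolment and at close-out.
- **Analysis.** Data analysis specifies, for these two outcomes, an exploratory ANCOVA "with the value at the end of treatment as dependent variable". The independent variables are group, baseline value and AN subtype. The weeks in between do not enter.
- **Comparison.** The same section analyses SUPA-Q with a linear mixed model on its repeated measures.
- **Population and missing data.** "All analyses will be done in the intention-to-treat population". The only imputation rule is limited to other endpoints: "For all feasibility outcomes, missing values will be imputed taking the reasons for dropout into account".
- **Use.** Under Objectives, the SDs of the full-scale trial's outcomes are to be estimated in order to size that trial. Weight gain and eating disorder psychopathology are among those outcomes.

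**The concern.** An ANCOVA on one end value can use only patients who have that value, unless something is imputed. Someone who completes weeks 1 to 3 and then leaves has given three informative measurements, and the stated model has no place for them. The article expects some dropout, since the close-out interview asks for reasons, but it gives no rate and no allowance in the 42 patients.

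Three things could suffer: the precision of the group comparison; its freedom from bias, if those who leave differ from those who stay in a way that depends on arm; and the SD passed on to the full-scale trial. The arms differ in simulated movement, so arm-dependent dropout is conceivable, though nothing in the article shows that it will occur.

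**Working it through.** **The plan's own figures.** The article gives no figure for this analysis. The one number that enters is the 42 patients, which comes from the adherence test in Table 1. That reproduces: exact binomial, 50% against 84%, n = 21 per arm, critical count 15, one-sided alpha 0.039, power 0.961. The other two rows also reproduce (n = 14, power 0.960; n = 16, power 0.959). This point changes none of them.

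**Step 1. Patients left in the end-value ANCOVA.** With a fraction d lacking the end value, 42 × (1 − d) remain, and the standard error grows by about 1/√(1 − d) against complete data. The values of d are assumed.

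| d | Patients left | SE factor |
|---|---|---|
| 5% | 39.9 | 1.03 |
| 10% | 37.8 | 1.05 |
| 20% | 33.6 | 1.12 |
| 30% | 29.4 | 1.20 |

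No analysis recovers all of this. Steps 2 and 3 show how much the weekly values recover.

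**Step 2. Illustration with a true effect of 0.5 SD.** Assumptions: baseline plus four weekly values, AR(1) correlation 0.8, effect growing linearly to week 4. The probability of leaving before each of weeks 2, 3 and 4 is 1/(1 + exp(2.8 + b·g·y)), where g = 1 in the VR arm and y is the last weekly value. With b = 0 the weekly probability is 0.057, so (1 − 0.057)³ = 0.84 complete.

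| b | Missing end value, VR / control | ANCOVA on completers | Using weekly values |
|---|---|---|---|
| 0 | 16% / 16% | 0.50 | 0.50 |
| 0.5 | 16% / 16% | 0.53 | 0.50 |
| 1 | 18% / 16% | 0.56 | 0.50 |
| 1.5 | 21% / 16% | 0.61 | 0.50 |

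The bias of the ANCOVA on completers is thus 0.03 to 0.11 SD when dropout depends on outcome in one arm, and zero when it does not depend on outcome. At n = 42 and b = 0 the empirical standard errors are 0.312 (completers), 0.303 (weekly values used) and 0.283 (nothing missing). The weekly values recover (0.312 − 0.303)/(0.312 − 0.283) = 0.31, about a third of the lost precision.

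**Step 3. Illustration with no true effect.** Assumptions: 21 per arm, four weekly visits, adjacent correlation 0.85, dropout driven by the last value in one arm only, unstructured covariance estimated from the data.

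| Overall loss | ANCOVA bias | ANCOVA SE relative to mixed model |
|---|---|---|
| 16% | −0.06 SD | about 1% larger |
| 28% | −0.09 SD | about 4% larger |
| 39% | −0.15 SD | about 8% larger |

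The mixed model stayed within 0.02 SD. A parallel run with the covariance treated as known, at about 15%, 25% and 35% loss, gave ANCOVA bias of −0.04, −0.05 and −0.09 SD. Its SE ratios were 0.294/0.285 = 1.03, 0.303/0.288 = 1.05 and 0.334/0.310 = 1.08; these flatter the mixed model slightly. With the same dropout mechanism in both arms, ANCOVA bias was about 0.01 SD or less.

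**Step 4. The SD.** Under similar assumptions the ANCOVA residual SD was 1-3% too low (mixed model about 1-2%), and the raw SD of completers 2-7% too low. A sample size scales with SD², so 3% low means 1 − 0.97² = 6% too few patients, and 7% low means 1 − 0.93² = 14%. For scale, the sampling error of a residual SD from 42 patients and four model parameters is about 1/√(2 × 38) = 0.11, or 11%, even with nothing missing.

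**The case against.** **Inference from silence.** A reader might infer that the plan commits itself to a complete-case analysis and so contradicts its own intention-to-treat statement. The article does not support that. It nowhere says that patients without an end value are excluded. Handling of missing values for exploratory outcomes is commonly left to the analysis plan, which is not shown. An ANCOVA with imputation from the weekly values would fit the text as written. The intention-to-treat label also fixes who is analysed and in which arm; it is not a missing-data rule. The mixed model itself omits anyone with no post-baseline value. This objection stands.

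**Little depends on it.** The analysis is exploratory. It enters neither the traffic-light decision nor the sample size. The between-group effect named under Objectives is on activity urges, which already has a mixed model. This stands too; for weight and EDE-Q the stated use is the SD.

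**Size.** In the known-covariance run the bias was 0.037/0.294 = 0.13 to 0.090/0.334 = 0.27 of a standard error, and it needs outcome-related dropout that differs by arm. The SD distortion is smaller than its own sampling error, and the mixed model corrects little of it. All of this stands.

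**Weight.** Patients are inpatients, and someone who stops VR but stays on the ward can still have an end weight on record. The point therefore bears mainly on EDE-Q and on early discharge.

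What the objection does not remove is that the choice of a single end value is stated, and that the weekly values are collected anyway.

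**Conclusion.** This is a worthwhile improvement rather than an error. As stated, the ANCOVA leaves unused the weekly EDE-Q and weight values of any patient who lacks the end value, unless imputation is added that the article does not mention for these outcomes.

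Under assumed dropout of about 15-40%, with within-patient correlations of 0.8 to 0.85:

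- the standard error is about 1-8% larger than with a model using the weekly values;
- the group difference is biased by roughly 0.03-0.15 SD if outcome-related dropout differs by arm, and hardly at all otherwise;
- the SD is about 1-7% too low.

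Dropout rate, mechanism and correlations are assumptions, since the article gives none. The improvement is optional: cheap and harmless, but with modest gain.

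**What to change.** In Data analysis, replace the end-value ANCOVA for BMI and EDE-Q by a linear mixed model for repeated measures on all weekly values:

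- week as a categorical factor, group by week, baseline value and AN subtype;
- correlated residuals within patient, with a simpler fallback structure named in advance for n = 42. An unstructured matrix for four weeks has 4 × 5/2 = 10 parameters. The fallback should still let the variance differ by week, so that the week-4 SD is estimated;
- report the week-4 group contrast and the week-4 residual SD. If close-out is a separate occasion from the end of week 4, say which one is the end-of-treatment value;
- keep the end-value ANCOVA as a sensitivity analysis.

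Alternatively, keep the ANCOVA as the main model and impute missing end values by multiple imputation from the weekly values.

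Either way, state that validity rests on missing-at-random. For the mixed model, also state that patients with no post-baseline value still do not contribute.

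The cost is analysis wording only, with no new data, visits or patients. The small downside is that a covariance structure must be chosen for a small sample.

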### Sample size

We employed a hypothesis testing approach for feasibility outcomes developed by Lewis *et al*^75^ to determine the sample size for the proposed feasibility trial. The rationale of this approach is that we determine a sample size that will allow us to test an observed feasibility outcome (eg, the adherence rate) against being in the defined red zone (unacceptable rate), based on an expectation of it being in the defined green zone (acceptable rate). In other words, we define a null hypothesis (the true feasibility outcome is not greater than the value demarcating the red zone) and an alternative hypothesis (the true feasibility outcome is greater than the value demarcating the red zone by magnitude of its difference towards the value demarcating the green zone). The study is then powered for a one-sided test to detect the difference between red and green zones. The amber zone (between red and green) is then split into two areas (major and minor amend) by the critical boundary of the corresponding test. For the proposed trial, α (one tailed) and β were set to.05.

The sample size calculations are listed in table 1 and were based on binomial exact tests (for tolerability and adherence rates) and a one-sample t-test (for acceptability means), respectively. The maximum sample size suggested by the Lewis approach is n=21 for evaluating adherence. We therefore targeted the recruitment of 42 patients to be randomly allocated to either the intervention arm or the control condition for an intention-to-treat analysis.

**Table 1 T1:** Sample size calculations

Feasibility outcome	Green zone	Red zone	Required n***
Acceptability (mean SUS across patients; SD=22.5^84^)	>70	<50	16
Tolerability (% of patients with SSQ mean≥40)	<60	>95	14
Adherence (% of patients with exposure mean≥12 min)	>84	<50	21

Note. Observed values in-between green and red zones provide no clear evidence for or against feasibility. This may signal to discuss steps to amend the trial procedures or re-evaluate progression criteria. *n designates the minimum number of recruited per study arm based on binomial exact tests (for Tolerability and Adherence rates) and a one-sample -test (for Acceptability means), respectively.

* n designates the minimum number of recruited patients per study arm based on binomial exact tests (for tolerability and adherence rates) and a one-sample t-test (for acceptability means), respectively.

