SSQSimulation Sickness QuestionnaireSUSSystem Usability Scale

For the analysis, the ‘traffic light’ approach will be applied. Each outcome is considered separately, and overall progression is then determined by the worst performing criterion (ie, go, if all outcomes are green; stop, if one outcome is red; amend, if one outcome is in the amber zone, but none are red). The probabilities for the wrong decision for the three feasibility outcomes with the planned sample size of 21 per arm is shown in table 2. Combined, the probability of falsely not progressing to the full trial is smaller than the sum of probabilities to falsely fall within the red zone and hence is smaller than 0.07%.

**Table 2 T2:** Probabilities for the wrong decision for the three feasibility outcomes

Probability if true value within	Red zone and falsely observed value within green zone	Green zone and falsely observed value within red zone
Acceptability	0.03%	0.03%
Tolerability	<0.01%	0.03%
Adherence	0.07%	0.01%

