### Assignment of interventions

Participants will be randomly assigned to either control or intervention conditions with a 1:1 allocation as per a specified randomisation schedule using permuted blocks of random sizes. Randomisation will be conducted by a staff member not involved in the recruitment or interviews. An independent researcher blinded to the patient’s intervention group will conduct all interviews and transfer the data into the database to avoid any detection bias. Blinding of the researcher administering the intervention was deemed infeasible, but patients will be blinded as per the different trial conditions, and we will encourage patients to not share their specific VR experiences with other therapists or patients. The researcher administering the intervention will otherwise not be involved in the patient’s overall treatment, such that performance biases are unlikely.

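### Tolerability is judged in all randomised patients with imputation, so patients who never start VR add sickness scores that cannot exist to the go/amend/stop rate

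*Protocol article*

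**What the plan says.** The Data analysis section fixes the population, "All analyses will be done in the intention-to-treat population", and then the missing-data rule, "For all feasibility outcomes, missing values will be imputed taking the reasons for dropout into account". The Sample size section links the two: the authors "targeted the recruitment of 42 patients to be randomly allocated to either the intervention arm or the control condition for an intention-to-treat analysis".

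Participant timeline says when the ratings arise: "After each session, patients will provide acceptability and tolerability ratings, and we will record the duration of completed exposure sessions". Outcomes adds that the session means are the dependent variables. The criterion in Table 1 is "Tolerability (% of patients with SSQ mean≥40"), with green below 60% and red above 95%. Data analysis compares the observed rate with these zones and attaches a Clopper-Pearson interval; a single red result decides against feasibility.

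The article names no exposed-patient set for tolerability. It states no imputed value for a patient without any session and no expected dropout rate.

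**The concern.** A patient can be randomised in the first week after admission and leave before session 1. That patient never wore the headset, so no VR side effect has occurred. The SSQ score is not an unobserved true value that imputation could approximate; it does not exist. Using the reason for dropout does not help, because VR sickness cannot be why someone left before any VR. A value on either side of 40 would be assigned without data.

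Adherence is different. Zero minutes is a genuine observation for a non-starter, and intention-to-treat is right there.

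Tolerability is one of three criteria, any of which can stop progression to the full trial, and its red margin is thin. A few scores from unexposed patients can decide the colour and enter the confidence interval as if they were observations.

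**Working it through.** **Inputs.** Error rates: "α (one tailed) and β were set to.05". Size: "with the planned sample size of 21 per arm". Patients are "randomly assigned to either control or intervention conditions with a 1:1 allocation", and 42/2 = 21, so recruitment contains no allowance for dropout. Tolerability zones (green below 60%, red above 95%) come from Outcomes and Table 1.

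**The plan's own figures reproduce.**
- Table 1, tolerability: the exact one-sided binomial test of 95% against 60% first meets both error limits at n = 14, with cut-off at most 11 patients at or above 40. P(X ≤ 11 | 14, 0.95) = 0.030 and P(X ≤ 11 | 14, 0.60) = 0.960.
- Table 2, tolerability at n = 21: P(X ≥ 20 | 0.60) = 0.033%, printed as 0.03%; P(X ≤ 12 | 0.95) = 0.00003%, printed as <0.01%.

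Table 2 therefore treats 20 of 21 as the smallest red result and assumes 21 real scores per arm.

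**Reach of the red zone in an arm of 21.** 20/21 = 95.24% is red; 19/21 = 90.48% is amber. With m non-starters imputed below 40, the highest possible rate is (21 − m)/21:

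| m | Highest rate | Tolerability red possible? |
|---|---|---|
| 0 | 21/21 = 100% | yes |
| 1 | 20/21 = 95.24% | only if all 20 exposed score ≥40 |
| 2 | 19/21 = 90.48% | no |

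For m = 2 with all 19 exposed patients at or above 40, the exposed-only rate is 19/19 = 100%, which is red. The Clopper-Pearson intervals also differ: 69.6% to 98.8% for 19/21, and 82.4% to 100% for 19/19.

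**If the arms were pooled (N = 42).** 40/42 = 95.24% is the smallest red result. Two imputed below 40 leave it just reachable; three give at most 39/42 = 92.86%.

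**Probability of a red result when the true rate among exposed patients is 95%.**
- No non-starters: P(X ≥ 20 | 21, 0.95) = 0.72.
- Two non-starters imputed below 40: 0.
- Two non-starters imputed at or above 40: P(X ≥ 18 | 19, 0.95) = 0.75.
- Exposed-only, n = 19: 0.95^19 = 0.38.

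With one non-starter imputed below 40, both approaches need 20 of 20 and give 0.95^20 = 0.36, so for the red zone they differ only from two onwards.

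**The green boundary moves too.** 12/19 = 63.2% is amber, but with two imputed below 40 it is 12/21 = 57.1%, green. Conversely, 10/18 = 55.6% is green, but with three imputed at or above 40 it is 13/21 = 61.9%, amber.

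**How often could two non-starters occur?** The article gives no rate. Taking a pre-exposure withdrawal probability d as an assumption, P(at least 2 of 21) = 1 − (1 − d)^21 − 21d(1 − d)^20. This is 6.5% at d = 2%, 28.3% at 5% and 63.5% at 10%.

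**The case against.** The strongest reply is that the harm rests on two things the article does not state: how many patients never start, and what value they receive. The imputation algorithm is normally left to the analysis plan, and a method that follows the exposed patients would score non-starters at or above 40 when all exposed patients do, leaving red reachable. This stands against any claim that the stop is disabled. It does not remove the point, because the contested item is the stated population and rule, not missing detail about the algorithm.

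Second, the imputation sentence may be aimed mainly at sessions missed after a patient has started. A reader might infer that starters who stop need no imputation because their endpoint is the mean of attended sessions. The article says only that means across sessions are used, so this inference is not supported. Reason-based handling is valuable for patients who stop because of sickness.

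Third, the consequence is limited. In the two-non-starter illustration the signal becomes amend, not go. Non-starters also count against adherence, and the worst criterion governs. This stands, although two non-starters alone still allow adherence of 19/21 = 90.5%, which is green, so adherence would not necessarily pick up the problem.

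Fourth, refusal before session 1 bears on acceptability, so removing non-starters from that criterion could bias it upwards. This stands, and is why acceptability is treated differently below.

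**Conclusion.** The point holds for tolerability. The stated rule places patients without any VR exposure in a side-effect rate that drives progression, using scores that cannot exist.

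Its size depends on assumptions. With at least two non-starters in an arm of 21, all imputed below 40, a tolerability stop becomes amber even if every exposed patient scores 40 or more. Judged over both arms pooled, it takes three; Tables 1 and 2 work per arm, while Data analysis does not say.

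A reader might infer that the plan makes a stop impossible. The documents do not support that: no imputed value or dropout count is given, values at or above 40 would push towards red, and adherence or acceptability can still stop progression. Nor do they support moving acceptability to exposed patients on the same grounds.

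**What to change.** In Data analysis:

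- **Tolerability:** evaluate the rate and its Clopper-Pearson interval in randomised patients with at least one started VR exposure. Keep the reason-based handling for patients who start and then stop, especially because of sickness. Show the all-randomised imputed rate as a sensitivity analysis.
- **Adherence:** keep all randomised patients and count non-starters as non-adherent. Report the number of non-starters and their reasons.
- **Acceptability:** keep the all-randomised analysis and add the exposed-only mean as a sensitivity analysis. The imputed value can matter here as well: an observed mean SUS of 49 in 19 patients (red) becomes (49 × 19 + 2v)/21 with two patients imputed at v, which is 44.3, 49.1 or 53.9 for v = 0, 50 or 100; the last is amber.

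**Cost.** The change is one of wording, but a smaller denominator makes the observed-rate stop stricter. With 20 exposed patients, 19/20 = 95.0% does not exceed 95%; with 19, 18/19 = 94.7%. Red then requires 100%, and its probability at a true rate of 95% is 0.38 with n = 19 against 0.72 with n = 21. The authors should accept this knowingly. The n of 14 in Table 1 is still met with up to 21 − 14 = 7 non-starters per arm, but that figure concerns the power of the test, not the reach of the stop rule.
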